## Abstract

**Background:**

Patients with irresectable stage III or metastatic melanoma presenting with poor prognostic factors are usually treated with a combination of immune checkpoint inhibitors (ICIs), consisting of ipilimumab and nivolumab. This combination therapy is associated with severe immune related adverse events (irAEs) in about 60% of patients. In current clinical practice, patients are usually treated with ICIs for up to two years or until disease progression or the occurrence of unacceptable AEs. The incidence of irAEs gradually increases with duration of treatment. While durable tumour responses have been observed after early discontinuation of treatment, no consensus has been reached on optimal treatment duration. The objective of the Safe Stop IPI-NIVO trial is to evaluate whether early discontinuation of ICIs is safe in patients with irresectable stage III or metastatic melanoma who are treated with combination therapy.

**Methods:**

The Safe Stop IPI-NIVO trial is a nationwide, multicentre, prospective, single-arm, interventional study in the Netherlands. A total of 80 patients with irresectable stage III or metastatic melanoma who are treated with combination therapy of ipilimumab-nivolumab and have a complete or partial response (CR/PR) according to RECIST v1.1 will be included to early discontinue maintenance therapy with anti-PD-1. The primary endpoint is the rate of ongoing response at 12 months after start of ICI. Secondary endpoints include ongoing response at 24 months, disease control at different time points, melanoma specific and overall survival, the incidence of irAEs and health-related quality of life.

**Discussion:**

From a medical, healthcare and economic perspective, overtreatment should be prevented and shorter treatment duration of ICIs is preferred. If early discontinuation of ICIs is safe for patients who are treated with the combination of ipilimumab-nivolumab, the treatment duration of nivolumab could be shortened in patients with a favourable tumour response.

**Trial registration:**

ClinicalTrials.gov ID NCT05652673, registration date: 08–12-2022.

## Introduction

In the past decade, the introduction of systemic therapy with immune checkpoint inhibitors (ICIs) and targeted therapy (TT) has revolutionized the treatment of advanced and metastatic melanoma and has significantly improved the perspectives of patients with this disease [1–3]. ICIs can block programmed cell death protein-1 (anti-PD-1: e.g. nivolumab or pembrolizumab) or cytotoxic T-lymphocyte-associated protein 4 (anti-CTLA-4: e.g. ipilimumab), thereby enhancing the T cell-mediated immune response [4]. By blocking the pathways that regulate the immune system, ICIs do not only stimulate T-cell mediated tumour lysis, but also increase the activity of the immune system against self-antigens, causing organ inflammation [5]. These immune-related adverse events (irAEs) can be severe, lifelong and often require immunosuppressive therapy [6]. Furthermore, the incidence of irAEs gradually increases with duration of treatment [7].

For the treatment of advanced melanoma, combination therapy with nivolumab and ipilimumab is preferred for patients presenting with poor prognostic factors, such as brain metastases, elevated LDH level and/or rapidly progressive disease [8]. In the pivotal randomized trial with three arms in treatment naïve patients with advanced melanoma, four cycles of combination therapy with ipilimumab and nivolumab, followed by maintenance treatment with nivolumab, was compared to nivolumab plus placebo and ipilimumab plus placebo [9]. Treatment was continued until disease progression, the occurrence of unacceptable AEs, or withdrawal of consent. In treatment naïve patients with irresectable stage III or metastatic melanoma, the combination of nivolumab with ipilimumab resulted in a response rate of 58% [9]. The median overall survival (mOS) for patients treated with combination therapy was 72.1 months [10]. In the Checkmate 069 trial, Hodi et al. showed that of 95 patients treated with the combination therapy, 56 (59%) patients had an objective response (CR/PR). At a median follow up of 2 years, 45 of 56 (80%) patients had an ongoing response [11].

Most patients who are treated with the combination therapy of ipilimumab and nivolumab have irAEs, varying from mild (grade 1–2, ~ 30%) to more severe (grade 3–4, ~ 60%) irAEs [12, 13]. Although rare, these irAEs can even be fatal (grade 5, < 5%). The higher rate of irAEs with the combination therapy is primarily caused by the addition of ipilimumab and usually occurs within six months after the start of treatment [13]. However, late-onset irAEs (> 1 year after start of therapy) have been reported in a subset of patients [14]. Most late-onset irAEs occurred in patients who continue with anti-PD-1 therapy, suggesting that continued exposure to anti-PD-1 increases the risk of late-onset irAEs. Therefore, a shorter treatment duration of maintenance treatment with anti-PD-1 may reduce the risk of (late) irAEs, without affecting efficacy [3].

In current clinical practice in the Netherlands, treatment is usually continued for up to a maximum duration of two years or until unacceptable irAEs or disease progression occurs. However, real-world outcomes in the Netherlands showed that treatment duration was often shorter than two years [15], because irAEs resulted in early discontinuation in ~ 50% of all cases. Another real-world study suggested that it is safe to discontinue anti-PD-1 earlier than the protocolized 2 years, regardless of the reason for discontinuation [16]. However, the optimal duration of maintenance treatment with nivolumab remains to be determined prospectively [17]. A shorter treatment duration would yield several major advantages since the current treatment schedule has a high impact on patients in terms of quality of life, healthcare resources and healthcare costs.

Previously, the first nationwide Safe Stop Trial in the Netherlands was initiated for patients with irresectable stage III or metastatic melanoma who were treated with anti-PD-1 monotherapy [18]. The design of this trial is comparable to the current Safe Stop IPI-NIVO Trial. The accrual for the first Safe Stop Trial has been completed successfully: the target number of 200 inclusions has been achieved and the study was considered safe according to the Data Safety Monitoring Board (DSMB). While the results of the first Safe Stop Trial are awaited, this study has shown that patients and physicians are willing to early discontinue ICI and has fuelled the demand for a similar trial for patients who are treated with ipilimumab-nivolumab combination therapy. This nationwide prospective interventional study investigates the safety of early discontinuation of maintenance treatment with anti-PD-1 in patients with irresectable stage III or metastatic melanoma who are treated with combination therapy of ipilimumab and nivolumab.

## Methods

### Primary objective

To assess the rate of ongoing response at 12 months after start of treatment in patients with advanced or metastatic melanoma who are treated with first-line ipilimumab and nivolumab and who discontinue treatment early upon achieving a (confirmed) CR or PR according to RECIST v1.1 [19]. Ongoing response is defined as ongoing complete response (CR) or partial response (PR) according to RECIST v1.1, without disease progression or melanoma-specific mortality. Death due to AEs without evidence of disease progression will not be considered progression.

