**Fig. 1 Fig1:**
[figure not shown]
Design of the Safe Stop IPI-NIVO trial. Patients can be included at (confirmed) response, between three and nine months after start of treatment with ipilimumab and nivolumab. Follow-up will be conducted according to standard of care. ^1^ Response evaluation according to RECIST v1.1 [19]. Abbreviations: CR/PR = complete response/partial response, SD = stable disease

In the Netherlands, all patients with advanced or metastatic melanoma are treated in one of the 14 designated Dutch melanoma centres. The current nationwide study will be executed in all 14 centres: Amphia Hospital, Breda; Amsterdam University Medical Centres – location VU, Amsterdam; Antoni van Leeuwenhoek—Netherlands Cancer Institute, Amsterdam; Erasmus Medical Centre Cancer Institute, Rotterdam; Isala Clinics, Zwolle; Leiden University Medical Centre, Leiden; Maastricht University Medical Centre + , Maastricht; Máxima Medical Centre, Veldhoven; Medical Centre Leeuwarden, Leeuwarden; Medical Spectrum Twente, Enschede; Radboud University Medical Centre, Nijmegen; University Medical Centre Groningen, Groningen; University Medical Centre Utrecht, Utrecht; Zuyderland Medical Centre, Sittard-Geleen. In February 2023, the first site (Erasmus Medical Centre Cancer Institute) opened for inclusion.

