### Study population

To be eligible to participate in this study, a patient must meet all of the following criteria:Age ≥ 18 yearsIrresectable stage III or metastatic melanomaAt least one cycle of ipilimumab-nivolumab for irresectable stage III or metastatic melanoma and considered to be a candidate for maintenance treatment with anti-PD-1;Previous systemic treatment, including immunotherapy, in the (neo)adjuvant setting is allowed;Response evaluation according to RECIST v1.1 using a diagnostic CT documenting target lesions every 12 (-2/ + 6) weeks from the start of ipilimumab-nivolumab:◦ for patients with CR on a diagnostic CT at response evaluation, a low-dose CT (which is usually part of ^18^FDG-PET/CT) is allowed at baseline◦ for patients with PR on a diagnostic CT at response evaluation, a low-dose CT (which is usually part of.^18^FDG-PET/CT) is allowed if sufficient target lesions are measurable for response evaluation according to RECIST v1.1 criteria In case of asymptomatic brain metastases prior to start of first-line ipilimumab-nivolumab, intracerebral tumour response should be confirmed using an MRI for response evaluation prior to inclusion in this study.Patients should be included after first CR/PR or first confirmed CR/PR according to RECIST v1.1Inclusion should take place no later than 5 weeks after first confirmed CR/PRIn case of SD at first response evaluation, confirmed CR/PR is required for inclusionEligible and willing to discontinue anti-PD-1 therapy within 4(+ 1) weeks after inclusion, i.e. first CR/PR or first confirmed CR/PRInclusion not later than nine months after start of treatment with ipilimumab-nivolumabPresence of MRI of the brain to screen for brain metastasis (prior to discontinuation of ipilimumab-nivolumab)Participants with previously locally treated brain metastases are eligible in case they meet the following criteria:◦ completely asymptomatic brain metastases at inclusion; an incidental epileptic seizure caused by a brain lesion is not considered an exclusion criterion◦ MRI of the brain at baseline and for response evaluation during treatment

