### Statistics primary endpoint

The rate of ongoing response at 12 months is the primary endpoint and will be estimated using the Kaplan–Meier method and its two-sided 95% confidence interval (CI). The study will be declared positive for the primary endpoint if the lower bound of the CI is higher than 82%. A Kaplan Meier plot will be generated to illustrate ongoing response over time. This analysis will not include patients who are lost to follow-up or whose death (without progression) was not melanoma related within the 12 months after start of treatment with ipilimumab and nivolumab. These patients will not be censored, but will be excluded from the analysis for the primary endpoint. For other endpoints, data from these patients will be included in the analyses when statistically feasible. Patients who are lost to follow-up are taken into account in the sample size calculation.

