### Sample size calculation

Sample size calculation was performed for the primary endpoint of ongoing response at 12 months. The sample size calculation of this trial is based on the results of the Checkmate-069 study [11] since this prospective study provides detailed patient-level data of first response and duration of response of patients who are treated with first-line combination therapy with ipilimumab-nivolumab. In the Checkmate-069, an ongoing response at 12 months was reported in 92% of patients who had a response within 3 months after start of treatment and were treated for at least 3 months. The hypothesis of the current trial is that the percentage of patients with an ongoing response at 12 months after start of treatment should not be more than 10% worse than the 92% reported in the Checkmate-069. Hence, the null-hypothesis is an ongoing response rate of 82%. Since the rate of ongoing response in the Checkmate-069 is based on a small subgroup, we assume that 90% (instead of 92%) of patients will have an ongoing response at 12 months after start of treatment as input for the alternative hypothesis.

For the sample size calculation, the one-sample log-rank test was used [20]. Given a one-sided type I error of 2.5%, 80% power, a null hypothesis of 82% ongoing response at 12 months, and an alternative hypothesis of 90% ongoing response at 12 months, a total of 20 events (i.e. patients with disease progression) are required. Given an inclusion period of 2 years and 1 year of additional follow-up, 77 patients need to be included to reach this number of events within a total study duration of 3 years. Taking a safety margin of < 5% (*n* = 3 patients) for loss to follow-up or not-melanoma related deaths, the total sample size was set at 80 patients.

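### Patients included after about month 3 add guaranteed event-free time that the 82% bar does not contain, so the ordinary 12-month Kaplan-Meier rate is too favourable against that bar

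*Protocol article*

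**What the plan says.** All references are to the protocol article.

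- **Clock.** Primary objective: "To assess the rate of ongoing response at 12 months after start of treatment in patients with advanced or metastatic melanoma".
- **Entry.** Study design, Fig. 1: "Patients can be included at (confirmed) response, between three and nine months after start of treatment with ipilimumab and nivolumab". Study population caps inclusion at nine months. It also requires a confirmed response where the first evaluation showed stable disease.
- **Scans before entry.** Study population: "using a diagnostic CT documenting target lesions every 12 (-2/ + 6) weeks from the start of ipilimumab-nivolumab".
- **Estimator and rule.** Statistics primary endpoint: a Kaplan-Meier estimate with a two-sided 95% interval, positive if the lower limit exceeds 82%. Patients lost, or dead of other causes without progression, within the 12 months are excluded rather than censored. "A Kaplan Meier plot will be generated to illustrate ongoing response over time". The section mentions no delayed entry, no landmark and no adjustment of the bar for time of entry.
- **Origin of the bar.** Sample size calculation: the reference is "92% of patients who had a response within 3 months after start of treatment and were treated for at least 3 months", and the hypothesis is that "an ongoing response at 12 months after start of treatment should not be more than 10% worse than the 92% reported". That gives the 82% null. The design assumes "an alternative hypothesis of 90% ongoing response at 12 months".

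**The concern.** Being in response is the condition for inclusion, so no included patient can have progressed before inclusion. For a month-3 entrant this does no harm, because the benchmark patients were selected in nearly the same way on the same clock: about 9 months remain in which a response can be lost. A month-6 entrant has only 6 such months and a month-9 entrant only 3, yet both are judged against a bar built on 9.

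Late entry follows from the inclusion rules. If confirmation comes at the next 12-weekly scan, entry at first confirmed response falls at about week 24 (5.5 months). Stable disease, then response, then confirmation falls at about week 36 (8.3 months), inside the cap. Study population also allows up to 4(+1) weeks after inclusion before stopping, so a month-9 entrant may have under two months off treatment when the primary endpoint is read.

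At stake is the trial's main claim. The bias favours declaring early stopping safe, and a single-arm trial has no control group to reveal it.

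**Working it through.** **1. The plan's own figures.** Hazard ratio = ln(0.90)/ln(0.82) = 0.531. Events = (1.960 + 0.842)² / (ln 0.531)² = 19.58, rounded up to 20. With exponential times, 2 years of uniform accrual and 1 further year, the event probabilities are 0.323 (null) and 0.189 (alternative), mean 0.256. Then N = 19.58/0.256 ≈ 76.5, rounded up to 77, plus 3 for losses = 80. The stated figures reproduce, but with every patient at risk from time 0, that is, with no allowance for delayed entry.

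**2. The decision rule as a count.** Losses within 12 months are excluded, so the Kaplan-Meier value at month 12 is a simple proportion. The article does not name the interval type. With n = 77, the lower limit exceeds 82% from 69 ongoing responses (plain), 70 (exact) or 71 (log-log).

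**3. Like-for-like null.** Let the true rate be exactly 82% at month 12 for patients in response at month 3. Assume constant hazard over months 3 to 12, unrelated to entry time. For entry at month m, the chance of being event-free at month 12 is 0.82^((12−m)/9):

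- m = 3: 0.82^(9/9) = 82.0%
- m = 6: 0.82^(6/9) = 87.6%
- m = 9: 0.82^(3/9) = 93.6%

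**4. Expected rate and false-positive rate.** The entry mixes are assumptions. Example: 0.6 × 0.820 + 0.3 × 0.876 + 0.1 × 0.936 = 0.848. For uniform entry, the average over months 3 to 9 is (0.936 − 0.820) / [(6/9) × 0.1985] = 0.877. The false-positive rate is the binomial probability of reaching 71, 70 or 69 of 77 at that rate.

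| Entry at months 3/6/9 | Expected rate | Log-log | Exact | Plain |
|---|---|---|---|---|
| 100/0/0% | 82.0% | 0.9% | 2.3% | 4.9% |
| 80/15/5% | 83.4% | 2.0% | 4.6% | 9.0% |
| 60/30/10% | 84.8% | 4.2% | 8.7% | 15.6% |
| Uniform, months 3–9 | 87.7% | 14.8% | 25.2% | 38% |

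The plain interval gives 4.9% with no late entry at all. Only the rise above the first row is due to entry time.

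**5. Hazard shape.** For the 60/30/10% mix, suppose the cumulative hazard splits 50/30/20% over months 3–6, 6–9 and 9–12. The exact-interval figure is then 13.7%. With a 20/30/50% split it is 5.6% (log-log 2.6%). The direction is unchanged.

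**6. Does delayed entry remove it?** In simulation under the same null, a left-truncated Kaplan-Meier estimate averages 82.0% for the 60/30/10% mix and 82.15% for uniform entry. False-positive rates with the log-log interval, ordinary against delayed entry:

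| Entry at months 3/6/9 | Ordinary | Delayed entry |
|---|---|---|
| 100/0/0% | 0.9% | 0.9% |
| 70/20/10% | 3.2% | 1.4% |
| 50/40/10% | 5.6% | 1.9% |
| One third each | 15.1% | 2.8% |

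**The case against.** **The benchmark shares the clock.** A reader might infer that all the time from treatment start to inclusion inflates the result. It does not. The 92% reference also counts from treatment start and is limited to responders within 3 months who were treated for at least 3 months. Those first 3 months are common to both sides, and if everyone entered at month 3 there would be no inflation. This stands and sets the limits of the point.

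**The estimate is right for what it literally describes.** The observed proportion is a valid estimate of ongoing response at 12 months from start in this mixture of entrants. That also stands: the fault lies in comparing it with a bar from a different mixture.

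**The size is not established.** The article gives no entry distribution. Scans about 12 weeks apart make entries cluster, and the nine-month cap, with scan intervals that may stretch to 18 weeks, limits month-9 entry. Uniform entry is therefore a poor description of the design, and its 15 to 38% should not be quoted as the expected error. The share entering near month 6 is nevertheless unknown and need not be small.

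**A much worse truth would not simply pass.** Under the mixes examined, a true month-3-to-12 rate of 74 to 79% would give an expected ordinary estimate of 82%. A reader might take that as a positive trial. It is not, because the lower limit must exceed 82%, which needs 69 to 71 of 77 (90 to 92%). At a true 78.7% with the 60/30/10% mix, a positive result occurs in 2.3% of trials (exact interval).

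**The analysis plan may deal with it.** A delayed-entry estimate is still a Kaplan-Meier estimate, so it would not conflict with the article. But the article itself fixes clock, estimator, exclusions and bar, and as stated they do not match.

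**Conclusion.** The concern holds for entry after about month 3. Each such patient brings guaranteed event-free time that the 82% bar does not contain, the effect is always towards a positive trial, and nothing in the article corrects it.

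No single error rate can be given. Against the one-sided 2.5% in the Sample size calculation, an assumed 20% of later entrants (80/15/5%) roughly doubles the error for each interval type, and 40% (60/30/10%) multiplies it about three- to fourfold. These figures rest on 77 evaluable patients, constant hazard, risk unrelated to entry time, and the assumed mixes.

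Melanoma-specific and overall survival use the same origin, so their curves also include time before inclusion in which death was impossible. They carry no threshold, and a reader should not infer a false-positive claim for them.

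**What to change.** In Statistics primary endpoint, estimate the 12-month rate with delayed entry: each patient joins the risk set at the inclusion date, the curve is read from month 3, and the 82% rule is applied to that estimate. State the assumption that risk at a given time since treatment start does not depend on when the patient entered. Do not label the result as conditional on response at month 3 for everyone, since patients with stable disease at the first evaluation were not in response then. Name the interval type, because the error rate depends on it. The log-log interval kept the error between 0.9% and 2.8% in the delayed-entry simulations above.

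Add two sensitivity analyses:

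- patients included at about month 3 only, which is the like-for-like comparison with the benchmark;
- ongoing response at 12 months after inclusion, reported without the 82% bar because that clock differs. Table 1 already schedules the scans.

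The same delayed-entry handling is advisable for melanoma-specific and overall survival.

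**Cost.** Analysis wording and one option in the survival procedure, using dates and scans already collected. The interval becomes somewhat wider. With the plain interval, power at a true 90% falls from about 64% (all entering at month 3) to about 56% for the 60/30/10% mix. It is lower with other intervals: before any change, 49% exact and 34% log-log.

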### Secondary objectives

To assess ongoing response at 24 months after start of first-line treatment with ipilimumab-nivolumabTo assess disease control (CR/PR) at the time of the response evaluationTo assess duration of response (CR/PR) measured until progressive/recurrent disease or melanoma related death, whichever comes firstTo determine melanoma specific survival measured from start of first-line treatment with ipilimumab-nivolumab until melanoma related deathTo determine overall survival measured from start of first-line treatment with ipilimumab-nivolumab until death by any causeTo assess the need and feasibility of restarting (systemic) treatment for melanoma after progressionTo assess disease control after restarting (systemic) treatment for melanomaTo assess impact of discontinuation of treatment on irAEsTo assess impact of discontinuation of treatment on health related quality of life (HRQoL)To assess the impact of early discontinuation of treatment on productivity, healthcare resources and hours of informal care

